**Sample size calculations**

Prelimiunary data from the PEDW dataset for the period 1998 to 2008 linked to 329,000 live births from WECC,

showed that there was a 1% chance of a renal admission before the first birthday, increasing to 2.8% by the

fourth birthday and 3.3% by the fifth birthday. The most common reasons for renal admission in children under 5 were urinary tract infection (ICD10 N39.0), non-specific renal condition (ICD10 39.9) and hydronephrosis (ICD10 N13.3). Admissions were more common in boys than girls, with a relative risk ratio of approximately 1.6. We will compare the rates of renal admissions between the 148 children with PCD and those without a marker. There will be 80% power for detecting a hazard ratio of at least 6.2 in admissions by the first birthday and for detecting a hazard ratio of 3.5 by the fourth birthday. Whilst these are large effect-sizes this study presents a unique opportunity to describe the natural histrory of PCD.

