**Project summary**

Long term kidney disease is one of the most common illnesses of childhood causing lifelong health needs. Babies born with abnormalities in the kidney are at risk of long-term kidney disease that may require

treatment such as dialysis and kidney transplant as they grow older. Opportunities for early diagnosis and treatment of kidney disease may reduce the severity of illness over time. In some pregnancies the marker pelvicalyceal dilatation, is detected in the baby’s kidney at the antenatal ultrasound scan. The meaning of this marker for the future health of the baby (for example the risk of urine infections or hospital admissions for kidney problems) is not known. There are no consistent guidelines about how to treat babies with this condition and so the identification of this marker can lead to anxiety for families and additional tests during pregnancy and after birth. We were funded by NISCHR to study the meaning of markers of uncertain significance (Welsh Study of Mothers and Babies). The study has recruited 21,106 pregnant women, with consent to follow-up the babies in future studies. There are 150 babies in our study with the kidney marker. We did not find any associations with immediate birth outcomes such as stillbirth, premature birth or genetic problems.

We propose a prospective electronic cohort study in which we will record link the data on babies already

recruited to the Welsh Study of Mothers and Babies (WSMB) with routinely collected health care datasets in

Wales to obtain follow-up data on hospital admissions and diagnoses in primary care during childhood. We will

describe the natural history of pelvicalyceal dilatation (5-9.9mm – PCD) and compare the pattern of hospital

admissions, interventions and procedures due to renal causes and the incidence of urinary tract infection during childhood between:

1. Babies with no markers and no major congenital malformations

2. Babies with a renal marker (PCD, 5 - 9.9mm) on the 18-20 week antenatal ultrasound scan

3. Babies with congenital hydronephrosis (>10mm) on the 18-20 week antenatal ultrasound scan

The information obtained will play an important role in facilitating the development of appropriate clinical guidelines and care pathways during pregnancy and after birth, including the appropriate use of medical interventions and treatment. We plan to publish results in peer review journals.

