**Study Design and Method**

**Study population and method**

This study will include babies born in Wales between 1st January 2009 and 31st December 2011 to mothers who consented to take part in the WSMB. All pregnant women receiving antenatal care in NHS Wales who had a mid pregnancy fetal anomaly scan provided by the NHS in Wales between 1st July 2008 – 31st March 2011 were eligible for recruitment to the study. Scan data were available for 74% of women in the study who had

singleton pregnancies (n=22,045). The maximum period of follow-up in this study will be five years, accounting for censoring by death or migration.

We will describe the natural history of PCD (5-9.9mm) and compare the pattern of hospital admissions for renal causes (using ICD10 codes N00–N99, Q60-Q64), interventions and procedures due to renal causes (using OPCS-4 codes), and the incidence of urinary tract infection (using Read codes) during childhood, in those with and without markers.

In order to carry out the analysis we will record link the babies in the WSMB to hospital admissions data and primary care data from general practices, with anonymised linkage of individual babies across the

datasets. This data linkage will be done by HIRU at Swansea University, using the SAIL databank.^21,22^ The data

contained within the databank are sensitive and HIRU have developed procedures to ensure the data is made

available for research whilst ensuring that individual confidentiality is protected, and have measures in place to ensure information governance standards are met.

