**Data sources**

We will use the following datasets that are available for research use in the Secure Anonymised Information

Linkage (SAIL) databank available for research use from the Health Information Research Unit (HIRU) at

Swansea University.

1. Data for admissions to NHS hospitals is contained in the Patient Episode Database for Wales (PEDW),

produced by the collation of information from clinical coding of hospital admissions by NHS Wales Informatics

Service (NWIS) who are mandated to do this in Wales.

2. Primary care data for patients are available from participating general practices that contribute data to the

SAIL databank. These general practices provide records of primary care activity with Read codes defining the

nature of this activity. The SAIL databank currently contains records of primary care activity for approximately

50% of general practice in Wales, but it is anticipated that this coverage will increase before the start of this

project in response to on-going work by HIRU to achieve this.

3. Data on the presence of major or minor congenital anomalies is reported to a stringently and comprehensively

validated registry in Wales – CARIS.

4. Data on deaths and causes of death from the Office for National Statistics (ONS) Mortality files.

5. The Welsh Demographic Service for data on migration out of Wales.

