**Statistical Analysis**

We will define three groups for analysis:

1. Babies with no markers and no major congenital malformations

2. Babies with a renal marker (PCD, 5 - 9.9mm) on the 18-20 week antenatal ultrasound scan

3. Babies with congenital hydronephrosis (>10mm) on the 18-20 week antenatal ultrasound scan

For groups 2 and 3 we will define three subgroups according to diagnosis at birth:

(a) no pathology (<7 mm)

(b) pelvicalyceal dilatation (7-9.9mm)

(c) confirmed congenital hydronephrosis (>10mm).

We will describe the natural history for babies in groups 2 and 3 including the detail of measurements of PCD at follow-up scans after birth using data from CARIS. We will describe the proportion of babies in sub-groups a, b and c, the proportion of children in these groups with any renal hospital admissions and/or linked procedures, and the incidence of urinary tract infections diagnosed in primary care.

For each baby we will define the length of follow-up and person-years at risk during the five-year study period,

accounting for censoring by death or migration. We will estimate and compare the proportion of hospital

admissions and the person-year incidence of urinary tract infections between groups 1, 2 and 3 according to

maternal age, parity, quintile of Townsend deprivation score quintile, gestational age, sex, and breast-feeding.

We will use time to event Cox’s regression analysis for the first admission to hospital for renal disease to obtain crude and adjusted hazard ratios for groups 2 and 3 as defined above compared to group 1; the adjustments will be for maternal age, parity, social deprivation, gestation, sex, birth-weight and breast-feeding.

We will model the number of urinary tract infections and hospital admissions for renal conditions separately using a negative binomial or Poisson model, depending on whether or not there is over-dispersion, allowing for the varying periods of time at risk for the children in the cohort, adjusting for the factors listed above.

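### The 80% power quoted for hazard ratios of 6.2 and 3.5 does not follow from 148 children compared with the full unmarked cohort; power there is about 93–97%

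*Protocol*

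**What the plan says.** All references are to the protocol.

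- **Sample size calculations, exposed group:** "We will compare the rates of renal admissions between the 148 children with PCD and those without a marker".
- **Sample size calculations, reference risk:** "there was a 1% chance of a renal admission before the first birthday, increasing to 2.8% by the". The 2.8% is the risk at age four; at age five it is 3.3%.
- **Sample size calculations, power:** "There will be 80% power for detecting a hazard ratio of at least 6.2 in admissions by the first birthday". At age four the corresponding hazard ratio is given as 3.5. The section then concedes that effects of this size are large.
- **Statistical Analysis:** Cox regression for first renal admission, giving "crude and adjusted hazard ratios for groups 2 and 3 as defined above compared to group 1". Group 1 is all babies with no marker and no major malformation. No matching or sampling of comparators is described.
- **Project summary:** "The study has recruited 21,106 pregnant women".
- **Study population and method:** "The maximum period of follow-up in this study will be five years, accounting for censoring by death or migration". No loss rate is given.

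The sample size section does not give alpha, sidedness, comparator number, formula, or any allowance for attrition or covariates.

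**The concern.** The protocol gives a specific numerical claim together with most of the inputs needed to check it, and the claim does not come out. With about 1.5 admissions expected among 148 children in the first year and about 9 expected at a hazard ratio of 6.2, 80% power looks too low.

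This is the protocol's only power statement, and the protocol itself concludes from it that only large effects are detectable. The results are meant to inform guidelines and information for parents, so readers may hold a null result against these hazard ratios. They would then treat hazard ratios of roughly 4.0–6.2 by the first birthday, and 2.7–3.5 by the fourth, as having less than 80% power when the planned comparison would have more.

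**Working it through.** **Inputs.** Exposed n1 = 148 and reference risks p0 = 0.01 (age one) and 0.028 (age four) come from the sample size section. The comparator number is not stated. I take n0 = 21,106 − 148 = 20,958, which is an upper bound because group 1 excludes babies with other markers or major malformations. Assumed: two-sided 5%, complete follow-up, no covariates. Risk in the exposed is p1 = 1 − (1 − p0)^HR.

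**Step 1: what reproduces the stated pair.** Schoenfeld: z = ln(HR)·√(D·π(1 − π)) − 1.96, with D = n1·p1 + n0·p0 and π the exposed fraction. With four comparators per case (n0 = 592, π = 0.2):

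- Age one, HR 6.2: D = 8.94 + 5.92 = 14.86; z = 1.825 × √(14.86 × 0.16) − 1.96 = 0.85; power 80.3%.
- Age four, HR 3.5: D = 14.00 + 16.58 = 30.58; z = 1.253 × √(30.58 × 0.16) − 1.96 = 0.81; power 79.1%.

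Solved for 80%, this gives 6.17 and 3.54. It is close to both figures, but for a sampled design that the protocol does not describe.

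**Step 2: the design described, pooled two-proportion formula.** z = [(p1 − p0) − 1.96·s0]/s1, with s0 the pooled and s1 the unpooled standard error.

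- HR 6.2: p1 = 0.0604, s0 = 0.00835, s1 = 0.01960; z = (0.0504 − 0.0164)/0.0196 = 1.74; power 96%.
- HR 3.5: p1 = 0.0946, s0 = 0.01372, s1 = 0.02409; z = (0.0666 − 0.0269)/0.0241 = 1.65; power 95%.

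**Step 3: plain check, exact binomial against a fixed reference.**

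- Age one: 148 × 0.01 = 1.5 expected. Five or more is significant (tail probability 0.017). At HR 6.2, 8.9 are expected and five or more occurs 95% of the time.
- Age four: 4.1 expected. Nine or more is significant (0.024). At HR 3.5, 14.0 are expected and nine or more occurs 95% of the time.

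**Step 4: other methods on the full cohort.**

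| Method | Power at 6.2 / 3.5 | HR with 80% power, age 1 / age 4 |
|---|---|---|
| Pooled two-proportion | 96% / 95% | 4.04 / 2.66 |
| Continuity-corrected | 94% / 93% | 4.46 / 2.81 |
| Arcsine | 95% / 94% | 4.67 / 2.87 |
| Mid-p exact | 95% / 94% | 4.57 / 2.80 |
| Fisher exact | 94% / 93% | 4.66 / 2.93 |
| Unpooled two-proportion | 73% / 79% | 7.0 / 3.55 |
| Schoenfeld, full cohort | 60–61% / 72–73% | 9.5–10.1 / 3.9–4.0 |
| Freedman | >99% / >99% | 3.3 / 2.4 |

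**Step 5: simulation of the planned type of analysis.** 148 vs 20,000, exponential times, 2,000 runs per point.

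| Test | Power at 6.2 | Power at 3.5 |
|---|---|---|
| Log-rank | 97% | 96% |
| Cox Wald | 97% | 95% |
| Cox likelihood ratio | 95% | 94% |

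The simulated 80% points are about 4.0–4.6 and 2.7–2.85. Simulation therefore agrees with the pooled, corrected and exact rows and contradicts the last three rows of the Step 4 table. One caution: under no effect at the 1% risk, the log-rank and Wald tests rejected in the upper tail in 5.6% and 4.6% of runs, against a nominal 2.5%; the likelihood-ratio test rejected in 1.4%. For age one, the upper end of the 4.0–4.7 range is thus the safer reading.

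**Step 6: sensitivity.**

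- n0 = 10,000: pooled power stays at 96% and 95%.
- 104 exposed children left (30% lost): 87–91% and 85–89%.
- Two-sided 1%: exact power 89% and 84%. Two-sided 0.1%: 68% and 65%.

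**The case against.** **The protocol's authors may have used a legitimate method on a different comparator group.** Step 1 supports this, so a reader who infers that no standard method returns both figures goes too far. What can be said is that none of the methods tried returns both for 148 children against the full unmarked group. If a 1:4 sample was used, the calculation describes a different study from the one in the analysis section. Even with 592 comparators, the pooled formula gives about 89–90% at the two hazard ratios.

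**The direction depends on the formula.** This is true: Schoenfeld on the full cohort suggests less than 80% power, and the unpooled calculation nearly matches the fourth-birthday figure. Simulation shows that both are poor approximations with 0.7% exposed and a large hazard ratio.

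**The 93–97% is a ceiling.** This stands. Censoring, incomplete linkage and adjustment for seven factors would lower power. The protocol gives no rates, so the reduction cannot be computed, but losing 30% of the exposed children would not bring power down to 80%.

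**About half of 148 was really meant.** A reader might infer this from the roughly 50% general practice coverage under Data sources. The protocol does not support it. That coverage concerns primary care records, not hospital admissions, and no single reduced number returns both figures under the pooled formula (70 children give 5.82 and 3.58).

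**It matters little.** Largely accepted. The cohort is already recruited and the study is presented as a description of natural history. The estimated hazard ratios and their precision will also show what a null result excludes, so the power sentence is not the only guide.

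**Conclusion.** The stated 80% is wrong as written for the design described. Under two-sided 5%, about 21,000 comparators and complete follow-up, power is about 93–97% at the stated hazard ratios. The 80% points are about 4.0–4.7 by the first birthday and 2.7–2.9 by the fourth. Alpha, sidedness and comparator number are assumptions; the result barely moves with comparator number.

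The error is conservative: the study can detect somewhat smaller effects than it says. A reader might infer that the protocol makes the study appear unable to see any hazard ratio between 3 and 6. It does not, since it already claims 80% power at 3.5 by the fourth birthday, and a hazard ratio of 3 by the first birthday is below 80% power on the recomputed figures too. No recruitment, stopping or analysis rule rests on the sentence. It is a reporting correction worth making, not a flaw in conduct.

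**What to change.** Recompute the sentence for the planned comparison of group 2 with the whole of group 1. Use one named method, and state alpha, sidedness, comparator number and any allowance for linkage loss or attrition.

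With 148 children fully followed and two-sided 5%, the pooled two-proportion formula gives 80% power at about 4.0 by the first birthday, 2.7 by the fourth and 2.5 by the fifth (3.3% risk). Log-rank simulation agrees for the first two. If an exact test is named instead, the first two values are about 4.6–4.7 and 2.8–2.9. Values from different tests should not be mixed in one range.

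If a sampled comparator group or a smaller linked number was intended, state it and reconcile it with the Statistical Analysis section.

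The cost is one paragraph, with no change to data collection, linkage or analysis.

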**Expected outputs of research**

The potential for maternal anxiety and difficulty in counselling women when markers are reported and the need for a consistent approach in the management of pelvicalyceal dilatation (PCD) is the principlal reason for this research. The impact of this work will be significant as information about the significance of renal ultrasound markers is not currently available. This work will address current gaps in the evidence-base about the health outcomes in infancy and childhood associated with renal pelvicalyceal dilatation. The findings from the study will further our understanding of the natural history of PCD and contribute significantly to the development of evidence-based clinical guidelines and care-pathways for the management of this condition. The findings will be used to provide accurate information for parents and avoid any unnecessary anxiety during pregnancy. Determination of the significance of this marker will also enable future cost-benefit analyses of reporting this marker and the utility of the marker in predicting health outcomes in children.

**Dissemination**

We will use standard dissemination strategies to make the study report available and present the findings from this study to relevant multi-disciplinary groups such as Antenatal Screening Wales, The National Specialist

Advisory Groups (NSAGs) to Welsh Government for Obstetrics and Paediatrics. We will also provide feedback to Health Boards and the Maternity Services Liaison Committee. We will also seek to disseminate study findings to pregnant women and parents of young children through our user representatives on the study steering group and the organisations they represent (e.g. The National Childbirth Trust) using appropriate websites and newsletters. In the Welsh Study for Mothers and Babies patient information leaflet we have told women that we will write to them about study findings in the future and we will do this by letter following the completion of the study. We will engage with the Children and Young People's Research Network and the Kidney Research Network (both NISCHR funded registered research groups). We will also present the findings of this study to academic audiences such as the British Maternal and Fetal Medicine Society, the British Association of Perinatal Medicine and The Royal College of Paediatricians. Each of these organisations have an annual conference in the United Kingdom and we will submit an abstract to present our work. We will also publish our work in peer-reviewed journals for dissemination to wider audiences.

*References*

3. NIHCE Clinical Guideline CG62: Antenatal care: Routine care for thehealthy pregnant woman. (March 2008) <http://www.nice.org.uk/cg62> (accessed 12.12.2012)

4. Welsh Study of Mothers and Babies. WAG/MRC Health Research Partnership. ([name] PI, [name], [name] co-PI) £199,323 April 2008- Dec 2012. Project ref: RFSHO7340

5. Welsh Study of Mothers and Babies. A population-based cohort study to investigate the clinical significance of Defined Ultrasound Findings of Uncertain Significance. Study report submitted to NISCHR December 2012

